#### Criteria for discontinuing or modifying allocated interventions

There are no specific criteria to discontinue or modify the allocated interventions. Participants can withdraw at any time. If they opt for withdrawing from the allocated treatment, they will receive standard NHS care.

#### Strategies to improve adherence to interventions

Participants are supported by a physiotherapist to remove their sling as they feel able or to maintain the sling in place for 4 weeks, depending on their allocated intervention. Participants are also supported by a physiotherapist to adhere to their prescribed exercise programme through the individual consultations and a study specific manual and website that detail the exercises and progressions. Participants are also asked to complete a sling use diary to record their time out of the sling at regular periods throughout the day for 4 weeks postrandomisation.

#### Relevant concomitant care permitted or prohibited during the trial

No concomitant care is prohibited in RaCeR 2. Other healthcare use will be collected during the trial, summarised and described.

#### Provisions for post-trial care

None beyond standard NHS care.

### Outcomes

Figure 2 presents the trial schedule of outcomes and assessments. On receipt of informed consent (online supplemental material 1), questionnaires are completed at baseline (before surgery), and at 12 weeks, 6 and 12 months after randomisation. At baseline, the questionnaire will include demographic data (eg, date of birth, sex and ethnicity), the SPADI and EuroQol five dimensions five levels (EQ-5D-5L).

10.1136/bmjopen-2023-081284.supp1Supplementary data

**Figure 2 F2:**
[figure not shown]
Trial schedule of assessments and outcomes. EQ-5D-5L, EuroQol five dimensions five levels; PI, principal investigator, QRI, quintet recruitment intervention, SPADI: Shoulder Pain and Disability Index.

#### Primary outcome measure

Shoulder pain and disability at 12 weeks postrandomisation will be measured using the SPADI. The SPADI is a validated self-report measure,^7^ it was more sensitive and responsive than the Oxford Shoulder Score in our RaCeR pilot and is the most used outcome measure in RCTs evaluating interventions for shoulder disorders.^6^

#### Secondary outcome measures

Shoulder pain and disability at 6 and 12 months postrandomisation will be measured using the total SPADI score.Health-related quality of life at 12 weeks, 6 and 12 months postrandomisation will be measured using the EQ-5D-5L.Time to return to usual activities, including work and driving, will be measured via self-report questionnaire at 12 weeks, 6 and 12 months.Healthcare resource use at 12 weeks, 6 and 12 months will be measured via self-report questionnaire.Rotator cuff repair integrity (evidence of full-thickness re-tear; yes/no) at 12 months will be assessed via diagnostic ultrasound scan.Number and nature of AEs at 12 weeks, 6 and 12 months will be measured via self-report questionnaire and clinician report.Self-report time out of the sling, measured in hours, over 4 weeks postsurgery via self-report diary.

#### Participants timeline

See figures 1 and 2.

### Sample size

The sample size calculation was based on total SPADI score at 12 weeks, powered to detect a minimal clinically important difference of 8 points between groups.^10^ Assuming an SD of 30 (the upper 80% confidence limit from our pilot study)^6^ at 90% power and significance level 5%, and using an independent t-test, results in 297 participants being needed per group (594 in total). However, using Analysis of Covariance (ANCOVA) (primary analysis), adjusting for the baseline SPADI score, where correlation (r) between baseline and 12 weeks=0.2 (data from pilot RaCeR RCT), the sample size was adjusted by (1-r2) plus one extra participant per group to 574 in total.^11^ In addition, adjusting for 10% non-response of SPADI questionnaire at 12 weeks, a target of 319 participants should be randomised per group, 638 in total.

### Recruitment strategies

#### The quintet recruitment intervention

We will implement the QRI aiming to optimise recruitment.^8^ Although our RaCeR pilot recruited 39% of those eligible, we anticipate challenges to recruitment in the main trial due to: (1) hesitance by surgeons to randomise patients (particularly older patients with larger rotator cuff tears) and (2) challenges in participants accepting the randomised allocation due to perceived risks of individualised EPDR.

The QRI has been applied to over 25 RCTs to date, leading to insights about individual and generic recruitment issues and the development of targeted strategies to improve recruitment rates.^12 13^ Rather than simply increasing the numbers of patients recruited, the QRI will aim to reduce ‘missed opportunities’ for enrolling eligible patients, while safeguarding informed consent. We will draw on insights from previous application of QRI methods in RCTs, and the latest recruitment-related evidence to develop materials and pre-emptive training which will support participant recruitment from the outset of RaCeR 2. Once sites open to recruitment, we will proceed to implement the QRI in two phases:

Phase 1: We will investigate recruitment issues that transpire ‘in real time’ throughout the remainder of the scheduled recruitment period. We will use mixed methods to investigate actual (rather than anticipated) issues hindering recruitment as the trial proceeds. Data collection will include:

Semistructured interviews with individuals involved in recruitment (‘recruiters’).Audiorecorded discussions between recruiters and potential participants about RaCeR 2.Mapping of recruitment pathways and screening log analysis.

Findings from these sources will be triangulated to generate an in-depth understanding of the ‘root-causes’ of key recruitment issues.

Phase 2: Using the results from phase 1, the QRI team will work closely with the TMG and patient and public involvement (PPI) group to design and implement ‘actions’ to optimise recruitment. Actions may be applicable to all sites, specific sites or individual recruiters and will aim to increase the number of eligible patients approached, and/or improve conversion rates while safeguarding informed consent. The QRI phases will run iteratively. New avenues of enquiry will emerge throughout the conduct of the QRI, through discussion in feedback meetings and continued monitoring of screening logs.

We will pay close attention to screening log data before/after QRI actions to formatively evaluate the impact of actions, and the need for further investigation (phase 1) or actions (phase 2). Part of the QRI will entail up-front training for site staff as they open to recruitment. This training will evolve to become increasingly focused as we develop our understanding of recruitment issues, with a view to ensuring sites that open in the latter stages of the trial benefit from the QRI insights that have emerged to date.

#### Assignment of interventions: allocation

#### Sequence generation

On completion of surgery, participants are randomised using minimisation. Participants are allocated on a 1:1 ratio, stratified by recruiting site and rotator cuff tear size; small (<1 cm), medium (1–3 cm), large/massive (>3 cm) or unknown.

#### Concealment mechanism

To ensure allocation concealment, randomisation is coordinated by Derby Clinical Trials Support Unit (DCTSU) remotely via an online randomisation system.

#### Implementation

The allocation sequence is generated by an online randomisation system. Following surgery, the local site team will explain to the participant their randomised allocation as well as other routine post-operative requirements. An exercise manual is provided to all participants, along with the sling diary. Participants will complete the diary with the amount of time (hours and minutes) they were not wearing the sling at regular periods throughout the day.

### Assignment of interventions: blinding (masking)

RaCeR 2 is an open-label RCT. No blinding of participants, clinicians, research team or oversight committees is in place.

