### Data collection, management and analysis

#### Plans for assessment and collection of outcomes

Following consent, the baseline questionnaire will be completed prior to surgery in-person or remotely. Completion of the baseline questionnaire will require input from local site staff and participants. The questionnaire will include the SPADI and EQ-5D-5L validated questionnaires and demographic data. The SPADI has 13 items divided into 2 subscales: pain (5 items) and disability (8 items). The responses are indicated on a Visual Analogue Scale (0=no pain/no difficulty and 10=worst imaginable pain/so difficult it requires help). The items are summed and converted to a total score out of 100, a high score indicates greater pain and disability.^7^ The EQ-5D-5L is a generic measure of health-related quality of life. It provides a single index value for health status that can be used in a clinical or health economic evaluation.^14^ The EQ-5D-5L consists of questions relating to five health domains (mobility, self-care, usual activities, pain/discomfort and anxiety/depression) and respondents rate their degree of impairment using five response levels (no problems, slight, moderate, severe or extreme problems). The EQ-5D-5L is the National Institute for Health and Care Excellence’s preferred measure of health-related quality of life in adults.

Follow-up questionnaires, including SPADI, EQ-5D-5L, self-report questionnaire for healthcare resource use, time to return to usual activities (including work) and any AEs, will be completed at 12 weeks, 6 and 12 months after randomisation (+4 weeks visit window to allow for reminders). This process will be coordinated centrally by the DCTSU. Follow-up questionnaires will be available in paper or electronic format. At 12 months following surgery, participants will be asked to undergo an ultrasound scan.

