#### Plans to promote participant retention and complete follow-up

If participants do not complete their questionnaires at the expected timepoints, they will be contacted at 2 weeks and a minimum data collection (SPADI and AEs) will be attempted via telephone at 3 weeks.

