#### Composition of the data monitoring committee, its role and reporting structure

Given the nature of RaCeR 2, a separate data monitoring committee will not be convened and the TSC will take on the data monitoring role, as agreed by the funder.

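### The blinding section makes no exception for outcome assessment, so the 12-month ultrasound re-tear reading is left open to knowledge of the allocation

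*Protocol article*

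**What the plan says.** The section on blinding declares the trial open-label and adds: "No blinding of participants, clinicians, research team or oversight committees is in place". It gives no exception for anyone who assesses an outcome and no reason for leaving assessors unmasked.

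The re-tear outcome is defined under Secondary outcome measures: "Rotator cuff repair integrity (evidence of full-thickness re-tear; yes/no) at 12 months will be assessed via diagnostic ultrasound scan". The section on collection of outcomes adds only that "At 12 months following surgery, participants will be asked to undergo an ultrasound scan". Neither section says who performs or reads the scan, or what that person knows. The article's list of strengths puts the scan forward as an addition to the self-reported measures.

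The primary outcome is collected differently. "The SPADI is a validated self-report measure", and "Follow-up questionnaires will be available in paper or electronic format". On follow-up, "This process will be coordinated centrally by the DCTSU". The telephone is a fallback: if a questionnaire is still missing after a reminder at 2 weeks, "a minimum data collection (SPADI and AEs) will be attempted via telephone at 3 weeks".

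**The concern.** Participants and treating physiotherapists cannot be blinded to when a sling comes off. That reason does not extend to someone reading a scan 12 months after surgery. A sonographer or radiologist is naturally a clinician, and a trials-unit caller is naturally research team, so both fall under the blinding statement as worded.

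Re-tear is where this matters most, for three reasons:

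- In the list of secondary outcomes, every other item is self-reported or clinician-reported. The scan is the one chance of an assessment independent of the participant and the treating team.
- The Introduction says that worry about re-tear is what supports the cautious approach. The re-tear comparison will therefore be read closely by those deciding whether to adopt early rehabilitation.
- The Economic analysis section names re-tear as an event in the long-term model, which is to be updated with trial data. A biased reading would carry into the cost-effectiveness result.

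A reader who knows the arm and expects more re-tears with early movement could over-call in that arm. One who favours the new approach could do the reverse. The bias could run either way, and the planned logistic regression cannot detect or remove it.

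**Working it through.** **1. The plan's own sample size, as a check.** Inputs from the Sample size section: difference 8, SD 30, power 90%, significance level 5% (two-sided assumed), r = 0.2, non-response 10%.

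- A two-sample t-test with d = 8/30 needs 296.5, so 297 per arm (594 in total).
- ANCOVA: 297 × (1 − 0.2²) = 285.12, rounded up to 286, plus 1 = 287 per arm (574).
- Non-response: 287/0.9 = 318.9, so 319 per arm (638).

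All three stated totals reproduce. Masking changes none of them.

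**2. Precision of the re-tear comparison.** The pilot rates of 30% (early) and 41% (standard) are in the Introduction. Scan attendance is not given; 80% is assumed, so 0.8 × 319 = 255 scans per arm.

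- SE = √(0.30 × 0.70/255 + 0.41 × 0.59/255) = √(0.4519/255) = 0.042
- 95% half-width = 1.96 × 0.0421 = 0.0825, about 8 percentage points
- An assumed 5-point over-call in one arm: 5/8.25 = 61% of the half-width, and 5/11 = 45% of the pilot difference

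| Assumed attendance | Scans per arm | Half-width (points) | 5 points as a share |
|---|---|---|---|
| 70% | 223 | 8.8 | 57% |
| 80% | 255 | 8.3 | 61% |
| 90% | 287 | 7.8 | 64% |

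At 255 per arm, 11 ± 8.3 gives an interval of about 3 to 19 points. If five extra points were called in the early arm, the rates would read 35% and 41%. The half-width is then 1.96 × √((0.2275 + 0.2419)/255) = 8.4 and the interval about −2 to 14, which includes zero. Over-calling in the standard arm would instead widen the apparent benefit from 11 to 16 points.

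**3. False-positive rate under differential reading.** Assume 287 readable scans per arm, a true rate of 35% in both arms, and an over-call of x in one arm. With p̄ the mean of the two observed rates, SE₀ = √(2p̄(1 − p̄)/287) and SE₁ = √([p₁(1 − p₁) + p₂(1 − p₂)]/287), the two-sided rejection rate is Φ((x − 1.96·SE₀)/SE₁) + Φ((−x − 1.96·SE₀)/SE₁).

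| Over-call x (points) | Rejection rate (nominal 5%) |
|---|---|
| 2 | 8% |
| 5 | 24% |
| 8 | 50% |
| 10 | 69% |

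**4. Telephone SPADI.** With 287 analysed per arm, the SE of the adjusted difference is 30 × √(1 − 0.04) × √(2/287) = 2.45 points. The shift in the mean difference, b, is the share collected by telephone times the differential interviewer bias. The rejection rate is 1 − Φ(1.96 − b/2.45) + Φ(−1.96 − b/2.45). Share and bias are both assumptions.

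| Telephone share | Bias (points) | Shift b (points) | Rejection rate |
|---|---|---|---|
| 10% | 2 | 0.2 | 5.1% |
| 10% | 4 | 0.4 | 5.3% |
| 30% | 2 | 0.6 | 5.7% |
| 30% | 4 | 1.2 | 7.8% |
| 30% | 8 | 2.4 | 16.5% |

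For biases of 2 to 4 points the shift is 0.2 to 1.2 points, against a target difference of 8.

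**The case against.** The strongest reply is that the article names neither the scan reader nor the callers. It condenses a full protocol that is not shown, and reader identity and request-form content are details that such an article may leave out. This stands as a limit on certainty: a reader might infer that the scan assessor is definitely unmasked, but the text supports this only as its natural meaning. It does not remove the point. The blinding statement is an explicit decision, and if the full protocol does mask the reader, the statement needs correcting.

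It can also be said that re-tear is a secondary outcome and that the attendance and over-call figures are invented. Both are true. The calculations show what a given bias would do, not that it exists.

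Several stronger readings are tempting but unsupported:

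- *Masking callers would protect the primary outcome.* SPADI is rated by participants who know their arm, mainly on paper or electronically. Masking callers affects only the telephone fallback and leaves participant reporting bias untouched.
- *Masking is free.* The documents give no cost. The trials unit coordinates both randomisation and follow-up, so callers without access to allocation may need some separation of roles, and participants may disclose their arm.
- *Surgeons are documented as seeing early rehabilitation as risky.* The section on the recruitment intervention attributes perceived risk to participants. Of surgeons it says that they may hesitate to randomise, particularly older patients with larger tears. The Introduction reports clinicians' general concern about re-tear, but nothing says what the scan reader believes.
- *Unblinded oversight lets by-arm results reach the trial team during recruitment.* The article does say that "the TSC will take on the data monitoring role". However, the committee has an independent chair, the funder agreed the arrangement, and the pilot interim analysis excludes between-group comparison of patient-reported outcomes. No section shows by-arm data reaching the trial team during recruitment.

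**Conclusion.** The point holds for the ultrasound reading. As written, the plan leaves the person who judges re-tear free to know the allocation, and the open-label design does not require this. Any resulting bias could run in either direction.

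Its size cannot be determined from the documents. Under the stated assumptions, a 5-point differential over-call is about 60% of the confidence interval half-width and would raise a nominal 5% error rate to about 24%; a 2-point over-call would raise it to about 8%. These figures rest on assumed attendance (80% for the first, 90% for the others), the pilot rates or an assumed common rate of 35%, and an unadjusted comparison of proportions rather than the planned logistic regression.

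Telephone collection is a lesser matter, likely to be small unless the telephone share and the interviewer bias are both large. The sample size and the primary analysis are not called into question.

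**What to change.** Amend the blinding section so that outcome assessment is an explicit exception to the open-label statement:

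1. State who performs and reads the 12-month scan, and that this person is not told the allocation.
2. Omit the allocation from the scan request form.
3. Ask participants not to disclose their arm at the scan.
4. Record any unmasking, so that its frequency can be reported by arm.

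As a lesser addition, have telephone collection of SPADI and adverse events done, where feasible, from a script by staff without access to allocation. Describe this as removing one small added source of bias, not as blinding the primary outcome.

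Scans, visits, treatment and sample size are unchanged. The cost is a revised request form, database permissions for callers with perhaps some separation of roles at the trials unit, and occasional accidental unmasking.

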### Data collection, management and analysis

#### Plans for assessment and collection of outcomes

Following consent, the baseline questionnaire will be completed prior to surgery in-person or remotely. Completion of the baseline questionnaire will require input from local site staff and participants. The questionnaire will include the SPADI and EQ-5D-5L validated questionnaires and demographic data. The SPADI has 13 items divided into 2 subscales: pain (5 items) and disability (8 items). The responses are indicated on a Visual Analogue Scale (0=no pain/no difficulty and 10=worst imaginable pain/so difficult it requires help). The items are summed and converted to a total score out of 100, a high score indicates greater pain and disability.^7^ The EQ-5D-5L is a generic measure of health-related quality of life. It provides a single index value for health status that can be used in a clinical or health economic evaluation.^14^ The EQ-5D-5L consists of questions relating to five health domains (mobility, self-care, usual activities, pain/discomfort and anxiety/depression) and respondents rate their degree of impairment using five response levels (no problems, slight, moderate, severe or extreme problems). The EQ-5D-5L is the National Institute for Health and Care Excellence’s preferred measure of health-related quality of life in adults.

Follow-up questionnaires, including SPADI, EQ-5D-5L, self-report questionnaire for healthcare resource use, time to return to usual activities (including work) and any AEs, will be completed at 12 weeks, 6 and 12 months after randomisation (+4 weeks visit window to allow for reminders). This process will be coordinated centrally by the DCTSU. Follow-up questionnaires will be available in paper or electronic format. At 12 months following surgery, participants will be asked to undergo an ultrasound scan.

#### Plans to promote participant retention and complete follow-up

If participants do not complete their questionnaires at the expected timepoints, they will be contacted at 2 weeks and a minimum data collection (SPADI and AEs) will be attempted via telephone at 3 weeks.

#### Data management

A secure electronic software platform (Dacima) will be used to store participant study data. Each participant is assigned a participant ID for use on study forms, other study documents and the electronic database.

#### Confidentiality

All documents will be stored safely in confidential conditions in accordance with the Data Protection Act 2018 and UK General Data Protection Regulation and retained according to national legislation.

### Statistical methods

#### Primary and secondary outcome analysis

Primary analyses will be conducted according to the intention-to-treat analysis group. ANCOVA will be used to compare total SPADI scores between individualised EPDR versus standard rehabilitation at 12 weeks after randomisation, adjusting for baseline SPADI score.

Among other secondary analyses, time to return to usual activities (work and driving) will be analysed using Kaplan-Maier curves and log rank test. Logistic regression will be undertaken to test the association between treatment groups and re-tear at 12 months. Linear regression will be used to test the association between treatment groups and time out of the sling over 4 weeks. Repeated measures ANCOVA will be used to test if any treatment effect exists and has been maintained up to 12 months in terms of SPADI and EQ-5D-5L scores. ANCOVA will be used to compare total SPADI and EQ-5D-5L scores between the treatment groups at 6 and 12 months adjusting for baseline scores. Safety analysis will be undertaken based on the per-protocol analysis group. The presence of AEs/serious AEs and problems after surgery will be compared between the two groups at 12 weeks, 6 and 12 months using χ^2^ test.

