### Study setting

A minimum of 24 NHS orthopaedic and physiotherapy services across the UK will be opened for recruitment. The internal pilot will last 6 months (June–November 2023). The trial monitoring group (TMG) in consultation with the trial steering committee (TSC) will assess study progress and decide on progression based on the criteria in table 1.

**Table 1 T1:** Internal pilot progression criteria

Progression criteria	Red (stop)* <66%	Amber (amend)† ≥66%–99%	Green (go)‡ 100%
Average recruitment rate/site/month	<0.7	0.7–1.0	1.1
Sites open	<12	12–17	18
Participants recruited	<50	50–96	97

*Red: halt, do not progress to main study.

†Amber: review areas of weakness and make amendments accordingly.

‡Green: no action required, continue to main study.

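### Allocation is minimised on site and tear size, but the primary ANCOVA adjusts only for baseline SPADI; if those factors are prognostic, its standard error is too large and its test conservative

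*Protocol article*

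**What the plan says.** Under Sequence generation, the protocol article states: "On completion of surgery, participants are randomised using minimisation". It continues: "Participants are allocated on a 1:1 ratio, stratified by recruiting site and rotator cuff tear size". Tear size has four categories: small, medium, large/massive and unknown. The Study setting section gives the number of sites: "A minimum of 24 NHS orthopaedic and physiotherapy services across the UK will be opened for recruitment".

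Under Primary and secondary outcome analysis, the primary comparison is an ANCOVA of total SPADI "at 12 weeks after randomisation, adjusting for baseline SPADI score". No other covariate is named. The Sample size section describes the same model, with baseline SPADI as the one adjustment variable and a correlation of 0.2.

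Tear size enters a model in one other place, an exploratory treatment-by-tear-size interaction under Methods for additional analyses. Site appears in no described analysis. The missing-data rule mentions a prognostic covariate belonging to the primary analysis but does not say which.

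**The concern.** Minimisation makes the arms alike on site and tear size. If those factors predict outcome, the treatment estimate varies less from trial to trial than it would under simple randomisation. A model that leaves them out does not know this. It keeps the between-site and between-tear-size variation in the residual, and its standard error describes a less balanced trial than the one that was run.

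At stake are the width of the primary confidence interval, the true level of the primary test, and some precision that the design has made available. The interval will be read against an 8-point difference, so needless width matters. Because the covariate is fixed in both the sample size and the analysis sections, this is a stated specification and not a detail left open.

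**Working it through.** **Inputs from the Sample size section.** Difference 8 points, SD 30, power 90%, significance level 5% (taken as two-sided, which reproduces the stated figure), baseline correlation r = 0.2, non-response 10%.

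**Reproducing the plan's figure.**
- Two-sample t-test (noncentral t): 297 per group, 594 in total.
- ANCOVA: 297 × (1 − 0.2²) = 285.12, rounded up to 286, plus 1 = 287 per group, 574 in total.
- Non-response: 287 / 0.90 = 318.9, so 319 per group, 638 in total.

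All three stated totals are reproduced.

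**The planned model.** SE = 30 × √(1 − 0.04) × √(2/287) = 2.454. Power = Φ(8/2.454 − 1.96) = 90.3%. The planned 90% therefore does not depend on adjusting for site or tear size.

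**Effect of omitting the factors.** Let R² be the share of residual variance (after baseline SPADI) explained by site and tear size together, and suppose that both are fully balanced. Then:
- true SD of the estimate = SE × √(1 − R²);
- type I error of the baseline-only model = 2Φ(−1.96/√(1 − R²));
- power of the baseline-only model = Φ((8/SE − 1.96)/√(1 − R²));
- power of the adjusted model = Φ(8/(SE√(1 − R²)) − 1.96).

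The article gives no R², so the values below are assumptions.

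| R² | Adjusted SE | Baseline-only SE too large by | Type I error, baseline-only | Power, baseline-only | Power, adjusted | Points forgone |
|---|---|---|---|---|---|---|
| 0 | 2.454 | 0.0% | 5.0% | 90.3% | 90.3% | 0.0 |
| 0.02 | 2.429 | 1.0% | 4.8% | 90.6% | 90.9% | 0.3 |
| 0.05 | 2.392 | 2.6% | 4.4% | 90.9% | 91.7% | 0.8 |
| 0.10 | 2.328 | 5.4% | 3.9% | 91.5% | 93.0% | 1.5 |
| 0.20 | 2.195 | 11.8% | 2.8% | 92.7% | 95.4% | 2.7 |

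In SPADI points, the 95% half-width of the planned model is 1.96 × 2.454 = 4.81. The adjusted half-width is 1.96 × 2.328 = 4.56 at R² = 0.10 and 1.96 × 2.195 = 4.30 at R² = 0.20.

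**Check by simulation.** Minimisation was simulated with 24 sites, four tear-size classes, 574 analysed and 4,000 runs per scenario. The 80% allocation probability, the class proportions and the equal split of R² between the two factors are assumptions.
- R² = 0.05: type I error 4.88% baseline-only, 5.35% adjusted; power 90.35% against 91.03%.
- R² = 0.10: mean model SE 2.456 against an empirical SD of about 2.36; type I error 3.9% against 5.2%; power 91.1% against 92.2%.
- R² = 0.20: type I error 3.1% against 5.2%; power 91.9% against 95.3%.

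The Monte Carlo standard error is about √(0.05 × 0.95/4000) = 0.34 points for type I error and √(0.92 × 0.08/4000) = 0.43 points for power. The pattern matches the formulas. Real minimisation balances imperfectly, which moves the level of the baseline-only test somewhat closer to 5% than the table shows.

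**The case against.** **The effect is conditional.** It exists only if site and tear size predict 12-week SPADI, and the article gives no figure for that. This stands. There are qualitative pointers: the trial team chose these factors for balancing, expects surgeons to hesitate over larger tears, and leaves the number of physiotherapy sessions open, so care may vary between sites. None of these supplies a variance share.

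**The sizing is coherent.** A reader might infer that power the trial has already paid for is being lost. The documents do not support that. The target of 638 was derived for baseline-only adjustment, and that model gives 90.3% power at R² = 0 and slightly more at every R² examined. What is forgone is additional power.

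**The error is in the safe direction.** A reader might also infer a biased treatment effect or too many false positives. Neither follows: the planned test is conservative and the interval slightly wide.

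**The secondary analyses.** It is tempting to extend the point to the re-tear analysis ("Logistic regression will be undertaken to test the association between treatment groups and re-tear at 12 months") and to the log-rank test. The article names those methods in a sentence each without fixing a covariate list, so its silence there is not a finding. Nor does it give a figure for how tear size relates to re-tear, or rank repair integrity above the other secondary outcomes. Adjusting a logistic model would also change the odds ratio being estimated, which is more than a wording matter.

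**An unseen document may already list the factors.** That is possible, and the unnamed covariate in the missing-data rule may hint at it. But this article describes the primary model in two sections, with the same single covariate each time. If another document says otherwise, the two should be brought into line.

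**Conclusion.** The point holds for the primary model, in conditional form. The specified ANCOVA does not reflect the allocation method. For an assumed R² of 0.02 to 0.20, its standard error is too large by 1.0% to 11.8%, its type I error is 4.8% to 2.8%, and it forgoes 0.3 to 2.7 points of power against the model that includes the factors. With R² = 0 there is no cost. These figures assume full balance on both factors among those analysed, two-sided testing and the article's own SD, correlation and analysed number.

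The planned power is not threatened, the sample size need not change, and no claim of bias or excess false positives is warranted. It is a modest weakness in the primary analysis with an almost free remedy.

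**What to change.** - State the primary model as 12-week SPADI on treatment, baseline SPADI, tear-size category (fixed effect) and recruiting site (random intercept, or fixed effect with small sites pooled).
- Use the same two factors in the 6- and 12-month SPADI ANCOVAs, which are also described as adjusting for baseline scores.
- Say which prognostic covariate the missing-data rule refers to, so that the list of covariates in the primary model is settled before analysis.

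Both factors are needed for randomisation, so no new data collection is required, and the target stays at 638. The cost is degrees of freedom. With 24 sites as unpooled fixed effects, site uses 23 and tear size 3, so residual degrees of freedom fall from 574 − 3 = 571 to 571 − 26 = 545, which is negligible. More than 24 sites would use correspondingly more; a random intercept or pooling would use fewer.
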